#### Sensitivity efficacy analysis

To assess the robustness of the main analysis, several sensitivity analyses will be performed:

- The same primary analysis will be performed on the Per-Protocol set (Statistical Table 20, Figure 3).
- In case of randomisation errors (patients not receiving the treatment attributed by randomisation) and/or stratification errors (patients not attributed to the correct strata at the time of randomisation), the primary analysis will be repeated, according to treatment attributed by randomisation and strata used for the randomisation). If no patient show randomisation or stratification errors, this sensitivity analysis will not be applicable.
- Cox-model regressions of overall survival adjusted for the stratification factors and prognostic factors on the FAS and PP sets, a two-sided 90% confidence interval of the hazard ratio of the treatment effect will be provided (Statistical Table 21, Figure 4)
  - Stratification factors:
    - Response to first line chemotherapy: objective response vs. stable disease,
    - Squamous vs. non-squamous,
    - Stage IV vs. recurrent stage I-III
  - Prognostic factors:
    - Level of tumor TERT expression: low vs. high,
    - Vaccine specific immune response status: naturally occurring response vs. absence of naturally occurring response

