#### Exploratory efficacy analyses

The following endpoints will be analysed in various exploratory analyses:

- Disease Control of Subsequent Second Line Treatments

Disease control rate defined as the ratio of the number of patients who had confirmed response (PR or CR) or stable disease (SD) according to the RECIST 1.1 criteria to the number of patients in analysis population (FAS, Per-protocol set, resp.). The disease control rates after the end of subsequent second line treatments will be compared between Vx-001 treated and placebo treated patients via two-sided Pearson’s chi-squared test (Statistical Table 25).

- Vaccine Specific Immune Response

Vaccine specific immune response (determined by the percentage of ARG-Vx001 specific T cells producing IFN-γ and/or perforin) will be evaluated by IFN-γ ELISpot® assay and perforin ELISpot® assay performed at baseline, after the second and sixth injection or end of treatment in case of the patient withdrawal from the study before or at Week 18 and from week 39, every 24 weeks.

The impact of the vaccine induced immune response on overall survival will be studied as follows:

Comparison of overall survival in patients with vaccine induced immune response detected after the second and sixth injection of Vx-001 (Statistical Table 26, Statistical Table 27, Figure 7, and Figure 8):

- - patients who received at least two and six injections of placebo, respectively,
  - patients randomised to Vx-001 who did not develop vaccine specific immune response after the second and sixth injections of Vx-001, respectively.

Comparison of overall survival in Vx-001-treated vs placebo-treated patients who had (Statistical Table 28, Statistical Table 29, Figure 9, Figure 10):

- a vaccine specific immune response before Vx-001 or placebo injection,
- high level of TERT expression or low level of TERT expression in their tumour biopsy.

These comparisons will be done using Kaplan Meier survival curves and two-sided Logrank test on FAS set.

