## Statistical/Analytical issues

### Adjustments for Covariates

All Cox models for all time-to-event endpoints, including for sensitivity analysis of the primary endpoint will be adjusted for the following stratification factors and prognostic factors:

- stratification factors:
  - Response to first line chemotherapy: objective response vs. stable disease,
  - Squamous vs. non-squamous,
  - Stage IV vs. recurrent stage I-III,
- prognostic factors:
  - Level of tumor TERT expression: low vs. high,
  - Vaccine specific immune response status: naturally occurring response vs. absence of naturally occurring response.

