### Handling of Dropouts or Missing Data

For the primary endpoint, if no information is available on patient survival, the patient will be censored at the time of the last information available. Also, for all time-to-event analyses the same censoring approach will be used. For the 12 months survival analysis (secondary efficacy endpoint), the missing efficacy data will be imputed using the worst case approach *(i.e.* “death” for the patients randomised in the Vx-001 arm and “alive” for the patients randomised in the placebo arm).

For all other variables except missing/incomplete dates (see below), missing data will be treated as missing and no imputation will be done.

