## Data handling conventions

### Baseline definitions

The measurements taken on baseline visit are assumed to be baseline values for the respective parameters.

Baseline visit, which takes place on day 1 of week 0, should be performed within 4 weeks after administration of the last cycle of first-line platinum-based chemotherapy.

The following characteristics will be measured at baseline visit:

- Physical examination and vital signs (blood pressure and pulse rate after 5 minutes sitting, body temperature and body weight, height)
- ECOG Performance Status.
- Electrocardiogram (12-lead ECG).
- Hematology.
- Clinical chemistry.
- Collection of blood sample for immunomonitoring. Samples will be collected before drug administration.

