# Derived data

| **Derived variable** | **Derivation algorithm** |
| --- | --- |
| Change from baseline to visit V (continuous) | Change from baseline of variable X=X_(Visit V)_-X_(Baseline)_   - Negative values indicate a decrease in X - Positive values indicate an increase in X |
| Percent change from baseline to visit V (continuous) | Percent change from baseline of variable X=100 *[X_(Visit V)_-X_(Baseline)_]/ X_(Baseline)_   - Negative values indicate a decrease in X - Positive values indicate an increase in X |
| First line treatment chimiotherapy | CDDP or Cisplatin/Docetaxel or Paclitaxel  CDDP/Gemcitabine  CDDP/Pemetrexed  CDDP/Vinorelbine (Navelbine)  CDDP/Etoposide  Carboplatine/Docetaxel or Paclitaxel  Carboplatine/Gemcitabine  Carboplatine /Pemetrexed  Carboplatine/ Vinorelbine (Navelbine) |

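### Every Cox model needs a baseline ELISpot result with no level for a missing one, so the adjusted survival hazard ratio is estimated on fewer patients than its FAS and PP labels imply

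*SAP*

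**What the plan says.** Section 5.3.1 (Adjustments for Covariates) is general: "All Cox models for all time-to-event endpoints, including for sensitivity analysis of the primary endpoint will be adjusted for" the three stratification factors and two prognostic factors. The prognostic factors are tumour TERT level, low or high, and "Vaccine specific immune response status: naturally occurring response vs. absence of naturally occurring response". Sections 5.2.4.2, 5.2.4.3 and 5.2.4.5 repeat this set for the survival sensitivity model, the time-to-treatment-failure model and the other exploratory models.

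Section 5.2.4.2 places the adjusted survival model among the analyses meant to test the robustness of the main result: "Cox-model regressions of overall survival adjusted for the stratification factors and prognostic factors on the FAS and PP sets", with a two-sided 90% confidence interval for the treatment hazard ratio.

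The immune response "will be evaluated by IFN-γ ELISpot® assay and perforin ELISpot® assay performed at baseline" (section 5.2.4.4). On the baseline blood draw, section 5.4.1 adds: "Samples will be collected before drug administration".

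Section 5.3.2 gives rules for censoring, for missing 12-month survival and for incomplete dates. For everything else, "missing data will be treated as missing and no imputation will be done". No section gives a level, a fallback covariate set or a rule for an assay that cannot be evaluated.

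**The concern.** The SAP never says that a patient without an assay result is excluded. Exclusion follows from combining its rules: a two-level covariate, no imputation, no level for a missing result, and a standard Cox fit in SAS (section 7), which omits any record with a missing covariate.

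This matters most for Table 21. The primary analysis in section 5.2.4.1 plans Kaplan-Meier curves and a log-rank test but no hazard ratio. Table 21 is therefore the only planned source of a survival hazard ratio with a 90% interval, and it is one of the checks on the primary result. As written, it is fitted on FAS and PP patients who also have a usable ELISpot and a TERT level. If it differs from the log-rank result, the cause may be covariate adjustment or a change of patients, and no planned analysis tells the two apart. A model with only the stratification factors would avoid the problem, because randomisation through the IWRS requires those factors for every patient. No such model is planned.

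**Working it through.** **Inputs from the SAP (revised sample-size calculation).** 12-month survival 43% on placebo and 58% on Vx-001, exponential; one-sided 0.05; 200 evaluable patients, 220 randomised, all assumed to be in the FAS; recruitment 39 months; primary analysis after 6 months of follow-up for all patients; stated power about 82.5%.

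**Assumed.** Uniform accrual, no drop-out, and a share *m* of patients without an evaluable pre-dose ELISpot. The SAP gives no value for *m*, so a range is shown. Loss is taken as unrelated to survival, so events fall in proportion to patients.

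**Step 1: hazard ratio.** ln(0.58)/ln(0.43) = 0.645, so |ln HR| = 0.438. The monthly hazards are −ln(0.43)/12 = 0.0703 and −ln(0.58)/12 = 0.0454.

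**Step 2: expected events.** With accrual A = 39 and minimum follow-up f = 6, the probability of death by the analysis is 1 − [exp(−λf) − exp(−λ(A+f))]/(λA). This gives 0.776 on placebo and 0.643 on Vx-001.
- 100 per arm: 77.6 + 64.3 = 141.9 events.
- 110 per arm: 85.4 + 70.7 = 156.1 events.

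**Step 3: reproduce the plan's figure.** Schoenfeld power = Φ(|ln HR|·√d/2 − 1.645). With d = 141.9 this is 83.2%, close to the stated 82.5%, so the model is adequate for what follows.

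**Step 4: remove patients without an assay.** Events become d(1 − m). The standard error of the log hazard ratio is about 2/√[d(1 − m)], so it rises by 1/√(1 − m) − 1. The 90% half-width is 1.645 times the standard error.

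| m (assumed) | SE rise | 220 patients: N / events / power / 90% half-width | 200 patients: N / events / power / 90% half-width |
|---|---|---|---|
| 0 | none | 220 / 156 / 86% / 0.263 | 200 / 142 / 83% / 0.276 |
| 10% | 5% | 198 / 141 / 83% / 0.278 | 180 / 128 / 80% / 0.291 |
| 20% | 12% | 176 / 125 / 79% / 0.294 | 160 / 114 / 75% / 0.309 |
| 30% | 20% | 154 / 109 / 74% / 0.315 | 140 / 99 / 70% / 0.330 |

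The 220-patient columns fit the FAS model and the 200-patient columns the PP model, because the plan ties 200 evaluable patients to the PP set. The power figures ignore any effect of covariate adjustment itself. A model that keeps every patient stays in the top row.

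**The case against.** The strongest reply is that nothing decisive rests on these models. The primary log-rank test uses no biomarker, and section 5.3.5 makes it the only basis for definitive conclusions. Section 5.2.4.2 also plans a PP log-rank test and, where randomisation or stratification errors occur, a repeat as randomised; neither needs the ELISpot. The SAP sets no power target for a sensitivity model. On the FAS base, a 10% loss still leaves about 83% power, roughly what the plan states for its primary analysis. All of this stands, and it limits the weight of the point.

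Sections 5.4.2.1 and 5.4.4 let a pre-baseline retest or an unscheduled value serve as baseline. That fills some gaps, but not for a patient with no evaluable pre-dose assay.

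A reader might infer more than the SAP supports, in four ways:
- **That the treatment comparison is biased.** The sample is drawn before dosing in a double-blind trial, so losses should be roughly balanced between arms. No bias is shown.
- **That adjustment and patient loss can never be separated.** An unadjusted Cox model or log-rank test on the same reduced set would separate them. It is not pre-specified, but nothing prevents it.
- **That TERT level will often be missing.** Central-laboratory TERT positivity with adequate tissue is an entry criterion, so large gaps are unlikely.
- **That Table 30 loses further patients through the first-line regimen list.** Section 8 has "CDDP/Etoposide" but neither carboplatin with etoposide nor an other group. An unlisted regimen is still a recorded value that needs a group, not a missing one. The SAP does not say that such patients are deleted, and nothing shows that there are any.

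**Conclusion.** The point holds as a weakness of the supportive analyses, and it should be corrected. As written, the Cox models labelled FAS and PP are fitted only on patients with an evaluable pre-dose ELISpot and a TERT level, and no Cox model on the full sets is planned. The cost is lost precision, and a robustness check and hazard ratio that come from a different set of patients than the primary result.

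The size depends entirely on an assay failure rate that the SAP does not give. Over an assumed 10% to 30%, the standard error rises by about 5% to 20%. Power of the FAS model falls from about 86% to between 83% and 74%, and that of a 200-patient model from about 83% to between 80% and 70%. If nearly all assays are evaluable, the effect is negligible. The primary conclusion is not at risk at any of these rates.

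**What to change.** In sections 5.2.4.2 and 5.3.1:
1. Make the main Cox sensitivity analysis a model with treatment and the three stratification factors, on the whole FAS and on the PP set, with its two-sided 90% interval.
2. Keep the biomarker-adjusted model as a further analysis, with a pre-specified not-evaluable level for baseline immune response and for TERT level, so that no FAS patient is dropped. Both are pre-treatment variables, so the extra level does not bias the randomised comparison.
3. Report the number of patients and events in each Cox model.

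The cost is SAP wording and a few lines of code before the first database lock, one or two extra model parameters, and one extra table. No new data are needed.

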**Missing or incomplete dates**:

For all listings, missing or incomplete dates will be left as they were recorded.

For calculation / sorting / assignation based on dates (e.g. treatment emergent AEs, concomitant medications…), the following rules will apply:

- The most conservative approach will be considered (i.e. if the onset date of an AE/concomitant medication is missing / incomplete, it will be assumed to have occurred during the study treatment phase (*i.e.* a TEAE for AEs) except when the partial onset date or other available data indicate differently (*e.g.* start date day missing, but month before the month of baseline date, or stop date before baseline date).
- Medical history or disease diagnosis with missing/incomplete date will be assumed to have occurred before any study treatment except when the partial onset date or other available data indicates differently.
- Assignations based on dates will be reviewed and confirmed or infirmed during the data review meeting

### Interim Analyses and Data Monitoring

No Data and Safety Monitoring Board has been set-up for this study.

The primary study analysis will be performed when all patients randomised will have reached 6 months follow-up. A long term follow-up analysis will be performed later when the follow-up of the study will be completed.

Two database locks will be performed. The first lock will occur for the primary study analysis. Before this first database lock, the data will be reviewed and the classification of protocol deviations will be done during the Blind data review meeting. After the first database lock, all study personnel will have access to unblinded data.

### Multicentre studies

This study is conducted in 76 sites in 8 European Union countries. With regards to the large number of sites compared to the planned number of patients, no adjustment for centre effect will be done.

Nevertheless, a descriptive analysis of efficacy by country will be done for the primary efficacy analysis and the survival analysis at 12 months. The countries where the number of randomised patients is less than 10 will be pooled in order to describe overall survival and survival at 12 months by country.

### Multiple Comparison/Multiplicity

The primary efficacy analysis will be the only analysis used to draw definitive conclusions on efficacy for the study. As a single primary efficacy analysis has been clearly pre-specified, there is no need to adjust for multiplicity of analyses.

All other inferential tests will only be provided with an illustrative purpose and will not be used to “rescue” the study in case the primary analysis is non-significant.

Consequently all other inferential tests, except the sensitivity analyses described in Section 5.2.4.2 above will be presented with a two sided significance level of 0.05 and with two-sided 95% Confidence Intervals. The sensitivity analyses will use a one sided significance level of 0.05 and two-sided 90% Confidence Intervals, for consistency with the primary efficacy analysis.

### Use of an "Efficacy Subset" of Patients

Two efficacy analyses populations were defined, the FAS and the PP. The definition of these populations is given in Section 3. The primary efficacy analysis will be conducted on the FAS. The PP population will be used to conduct a sensitivity analysis and assess the robustness of the primary efficacy analysis conclusions. Any substantial difference between the two analyses will be explored and discussed.

Patients who did not receive at least one dose of investigational product and patients who violate a major entry criterion (as defined in section 3.2) will be exclude from the primary efficacy analysis

(Full analysis set, FAS) provided it can be clearly justified that their exclusion does not introduce bias.

### Active-Control Studies Intended to Show Equivalence

Not applicable.

### Examination of Subgroups

No specific subgroup analysis will be done but descriptive statistics will be presented on each stratification factors subgroups for the primary endpoint *i.e*.:

- - Response to first line chemotherapy: objective response
  - Response to first line chemotherapy: stable disease,
  - Squamous
  - non-squamous,
  - Stage IV
  - recurrent stage I-III,

The same descriptive analyses will be performed for each prognostic factors subgroups i.e.:

- - Level of tumor TERT expression: low
  - Level of tumor TERT expression high,
  - Vaccine specific immune response status: naturally occurring response
  - Vaccine specific immune response status: absence of naturally occurring response.

## Data handling conventions

### Baseline definitions

The measurements taken on baseline visit are assumed to be baseline values for the respective parameters.

Baseline visit, which takes place on day 1 of week 0, should be performed within 4 weeks after administration of the last cycle of first-line platinum-based chemotherapy.

The following characteristics will be measured at baseline visit:

- Physical examination and vital signs (blood pressure and pulse rate after 5 minutes sitting, body temperature and body weight, height)
- ECOG Performance Status.
- Electrocardiogram (12-lead ECG).
- Hematology.
- Clinical chemistry.
- Collection of blood sample for immunomonitoring. Samples will be collected before drug administration.

### Retest, Outliers

#### Retests

The retests will be managed as follow:

- Any retest before baseline : the last available value before baseline will be used as the baseline
- Any other retest: data will be reviewed and decision will be made during the blind review on the basis of the following rules:
  - Retest on efficacy data: non-missing value the closest to the scheduled visit will be used
  - Retest on safety data: the worst recorded value will be used

#### Outliers

All outlier data will be reviewed during the data review meeting and decisions regarding their use in the statistical analyses will be made.

### Windows for time points

Patients have to visit the clinic/institution for investigational product administration and assessments according to the Flow Chart and Schedule of Assessments (see section 2.3.3) Permitted deviations from the predetermined dates of visit (due to weekends, public holidays etc) may be as follows:

- Screening period: can start during the first line chemotherapy and should be completed at the latest 3 weeks and 4 days after administration of the last cycle of first-line platinum-based chemotherapy,
- Baseline, randomization and first dose of vaccination: up to 4 weeks and 4 days after the last administration of the first-line chemotherapy
- Doses 2-6 of vaccination: ± 4 calendar days
- Week 18 : ± 4 calendar days
- Doses 7 to end of study vaccination: ± 14 calendar days
- End of study treatment visit: ± 4 calendar days
- Survival follow-up contact: ± 28 calendar days

Any deviations greater than the above, will be regarded as a protocol deviation. The sponsor will have to be notified, to decide whether the deviation constitutes a minor or major protocol deviation. If required, the Steering committee will be consulted. When the permitted deviations are applied, or when the study treatment has to be postponed, the next study visit should be carried out at a time that allows a minimum of 14 days between 2 vaccinations (from doses 1 to 6 of vaccination) and a minimum of 2 months between 2 vaccinations (from doses 7 to the end of study treatment). In addition, effort should be made to keep up with the schedule, based on the date of first investigational product administration (first dose).

### Unscheduled visits

Unscheduled visit measurements may be used to provide a measurement for a baseline or endpoint value if appropriate according to their definition. Other unscheduled visits data will not be analysed, but corresponding data will be presented in the individual data listings and any relevant safety data will be described in the CSR.

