### Adverse events

Any untoward medical occurrence in a patient or clinical investigation patient administered a pharmaceutical product and which does not necessarily have to have a causal relationship with this treatment.

An Adverse event (AE) can therefore be any unfavorable and unintended sign (including an abnormal laboratory finding), symptom, or disease (new or exacerbated) temporally associated with the use of a medicinal product, whether or not considered related to the medicinal product. The events occurring during pre-and post-treatment periods will also be designated as AEs. Therefore, reporting of such events, AEs and SAEs, will commence when the patient is enrolled into the study (date of signature of the informed consent) up until 4 weeks after the end of the treatment visits.

Adverse events (AE) will be coded using the latest available version of the Medical Dictionary for Regulatory Activities (MedDRA) and will be classified by MedDRA Preferred Term (PT) and System Organ Class (SOC).

Treatment Emergent Adverse Events (TEAE) will be defined as any adverse event that occur or worsen after the start of the study treatment *i.e.:*

- An AE that was not present prior to receiving the beginning of study treatment, or
- An AE that was present prior to receiving beginning of study treatment but which made the condition worse after the study treatment started.

Serious adverse events (SAE) are those AE that put the life of the patient at risk or that cause serious or permanent damage to the patient's health. An AE is to be recorded and reported as SAE in the event of any of the following:

- AE results in death
- AE is life-threatening
- AE requires hospitalisation or prolongation of existing hospitalisation
- AE results in persistent or significant disability or incapacity
- AE is a congenital anomaly or birth defect.
- AE is another medically important condition: This refers to an AE that may not be immediately life-threatening or results in death or hospitalization but may jeopardize the patient or may require intervention to prevent one of the outcomes listed above. Based on medical and scientific judgment (according to the investigator and or the sponsor) this should usually be considered serious.

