**Adverse events tabulations:**

Tabulation of adverse events will present for each cell the following information: number of patients with at least one occurrence of the event, corresponding percentage and number of events (if relevant). The following tables will be produced for all subjects included in the SAF population as well as by treatment group:

Summary table of adverse events (Statistical Table 32):

- Any AE
- Any TEAE
- Any drug-related TEAE
- Any TEAE leading to study drug discontinuation
- Any SAE
- Any treatment emergent SAE

For each category of the summary table of AE, 95% confidence intervals will be calculated for the incidence rates in each treatment group, together with a confidence interval for the treatment group difference in incidence rates.

A descriptive analysis will be performed for TEAEs. Global frequencies of SOC and PT will be calculated for:

- All TEAE by SOC an PT (Statistical Table 33)
- All not related TEAEs (*i.e.,* causality relationship to study drug is Not related) by SOC and PT (Statistical Table 34)
- All related TEAEs (*i.e.,* causality relationship to study drug is Possible, Probable or Definite) by SOC and PT (Statistical Table 35)
- All TEAEs by SOC and PT and by severity grade (Statistical Table 36)

Multiple counts within a PT or SOC (repeated or different included terms or changes in descriptors) will be considered only once per subject for the calculation of frequencies.

Depending on the number of TESAEs, similar tables as described above for TEAEs may be produced for TESAEs (Statistical Table 37, Statistical Table 38, Statistical Table 39 and Statistical Table 40). If the number of TESAEs is small, no specific tabulation of TESAEs will be produced.

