#### Laboratory safety variables

Hematology and clinical chemistry data will be summarized at each scheduled assessment and presented by NCI CTCAE toxicity grade (version 4) (see Appendix 7: section 10.7).

In case of relevant abnormalities on the laboratory variables detected from statistics tabulations, the data will be presented graphically using a plot of mean level versus time by treatment group and/or a Pre/post treatment scattergram for each relevant laboratory variable (Figure 9 and 10 respectively).

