**Qualitative descriptive statistics:**

- Qualitative descriptions statistics will be tabulated for each laboratory variable at each time over the course of the study overall and by treatment group (Statistical Table 42 and 45):
  - By clinical significance (normal, abnormal NCS, abnormal CS)
  - By CTCAE grade
- Shift Tables between CTCAE grade or clinical significance for each laboratory results comparing baseline to each visit (Statistical Table 43 and 46).

A listing of all safety-related laboratory tests (Listing 16.2.8.1 and 16.2.8.3) will be prepared, presenting patient id, identification of time point, Age, Sex, weight and IMP dose, identification of laboratory test, result, flagged as abnormal when abnormal and normal range when available and relevant, toxicity grading when available. This listing will be presented by study site and by study treatment.

A patient listing of abnormal laboratory values will also presented (Listing 16.2.8.2 and 16.2.8.4)

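### A worst laboratory grade found only at an unscheduled visit can be absent from the by-arm laboratory grade and shift tables, and the SAP does not say when such a result counts as a retest

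*SAP*

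**What the plan says.** Section 5.4.4 (Unscheduled visits) opens with an exception: "Unscheduled visit measurements may be used to provide a measurement for a baseline or endpoint value if appropriate according to their definition". Everything else falls under the next rule, "Other unscheduled visits data will not be analysed", with the qualification that "corresponding data will be presented in the individual data listings and any relevant safety data will be described in the CSR".

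The laboratory part of the safety analyses starts from the scheduled visit: "Hematology and clinical chemistry data will be summarized at each scheduled assessment and presented by NCI CTCAE toxicity grade (version 4". Tables 41 and 44 give quantitative summaries over time. Tables 42 and 45 give clinical significance and CTCAE grade at each time. Tables 43 and 46 are the shift tables, described as "Shift Tables between CTCAE grade or clinical significance for each laboratory results comparing baseline to each visit". Appendix 1 lists no other laboratory table.

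Section 5.4.2.1 (Retests) handles repeat tests after baseline at the blind review, under the rule "Retest on safety data: the worst recorded value will be used".

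**The concern.** The SAP's safety objective is a comparison between arms, and laboratory evaluation is one of its named components. A reader of the clinical study report will want to know how many patients in each arm ever reached a high CTCAE grade. By-visit tables do not answer this directly, and the rule in 5.4.4 can also remove the result that carried the highest grade. Leaving results out can only lower a patient's highest visible grade or leave it unchanged, so any error is towards under-reporting.

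The retest rule takes the worst safety value, while the unscheduled-visit rule sets such values aside. Nothing says which applies when a blood test is repeated between visits, so two programmers could build different tables from the same data.

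**Working it through.** The SAP states no figure on this point, so the check is a reading of the rules against each other. Take a grade 3-4 laboratory value observed only at an unscheduled visit and follow it through the planned outputs.

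1. **Baseline/endpoint exception (5.4.4).** The value is post-baseline, so it could enter only as an endpoint value. The Laboratory endpoints section lists parameters and visit weeks. It defines no on-study maximum or worst value that an unscheduled result could supply, so the exception does not clearly apply.
2. **Retest rule (5.4.2.1).** If the value is classed as a retest, the worst-value rule can bring it into the tables, subject to blind review. If not, 5.4.4 applies and it is not analysed. The SAP has no definition that decides between the two.
3. **Outputs, if it is not a retest:**

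| Output | Does the value enter? | By-arm summary? |
| --- | --- | --- |
| Tables 41, 44 (quantitative) | No | Yes |
| Tables 42, 45 (grade by visit) | No | Yes |
| Tables 43, 46 (shift to each visit) | No | Yes |
| Listings 16.2.8.1 to 16.2.8.4 | Yes | No count |
| Study report text | If judged relevant | No count planned |
| Tables 33 to 36 (TEAEs) | Only if reported as an AE | Yes |

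4. **Size.** The share of high grades lost through 5.4.4 depends on how often blood is drawn off schedule and what those draws show. The SAP gives neither. It also contradicts itself on the scheduled draws in the first 18 weeks. The flow chart marks post-baseline haematology and chemistry at weeks 9 and 18 (2 draws). The Laboratory endpoints section lists weeks 3, 6, 9, 12, 15 and 18 (6 draws). These passages must be reconciled. No loss figure can be derived from them.

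**The case against.** The strongest defence is that the plan has other routes for these values. Its adverse event definition covers "any unfavorable and unintended sign (including an abnormal laboratory finding), symptom, or disease", with no restriction to scheduled visits. Table 36 counts treatment-emergent events by severity grade and arm, and Table 32 gives confidence intervals for between-arm differences in the summary categories. All laboratory tests are listed, with toxicity grade when available, and abnormal values have their own listings. A repeat of an abnormal test is naturally a retest, for which the worst value is used. No safety hypothesis test is planned, so the laboratory tables are descriptive.

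Much of this stands, and it rules out several stronger readings:

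- *Unscheduled results are excluded from every analysis.* They are not. Section 5.4.4 excepts baseline and endpoint values, and retests follow their own rule.
- *High grades disappear from the safety tables altogether.* They do not. A laboratory abnormality reported as an adverse event is counted by arm whenever it was found. The gap is confined to the laboratory tables.
- *The two rules contradict each other.* The text shows only that the boundary between them is undefined.
- *The visit spacing gives the percentage lost.* It does not. Suppose an abnormality lasts one week (assumed) with random onset. Its chance of coinciding with a scheduled draw is 2/18 = 11% on the flow chart and 6/18 = 33% on the Laboratory endpoints list. Apart from depending on which schedule is used, this describes how sparse the scheduled sampling is. An episode that falls between scheduled draws is not thereby detected at an unscheduled one, so the calculation says nothing about data discarded under 5.4.4.

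The defence does not close the gap. The adverse event route depends on the investigator reporting the finding, whereas graded laboratory tables are useful because they do not. Listings and report text preserve the value but give no count by arm.

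**Conclusion.** The point holds for the laboratory grade tables (42, 45) and shift tables (43, 46). As written, the SAP can leave a patient's worst laboratory grade out of them, and it plans no worst-grade table that would recover it. It also leaves open when an unscheduled result is a retest.

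The size is unknown, and the SAP does not show whether the loss would differ between arms. The conclusion assumes that each visit in the shift-table description means each scheduled visit, which the opening sentence of the laboratory section supports. It also assumes that the endpoint exception does not reach an undefined on-study maximum. The matter affects descriptive safety reporting only and does not touch the primary analysis. It is worth correcting because the correction is cheap and the data are already to be listed.

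**What to change.** - Keep Tables 41 to 46 by visit. A worst-grade summary tends to rise with the number of draws, so the by-visit view should stay beside it.
- Add two tables by arm, one for haematology and one for chemistry, shifting from baseline to worst post-baseline CTCAE grade per patient and using scheduled, repeat and unscheduled results.
- Amend 5.4.4 to say that unscheduled safety results enter worst-grade summaries.
- Reconcile 5.4.4 with 5.4.2.1 by defining when an unscheduled result counts as a retest and which rule then governs the by-visit tables.
- Reconcile the laboratory schedule in the flow chart with that in the Laboratory endpoints section.

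The cost is two extra tables and short text amendments, with no new data collection. The reported laboratory toxicity rate may be slightly higher.
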